## Abstract

**Background:**

Carotid artery stenting (CAS) and carotid endarterectomy (CEA) are alternative strategies for stroke prevention in patients with atherosclerotic carotid disease. CEA has been considered the first-line treatment for carotid stenosis worldwide, and the safety and efficacy of CAS compared to CEA remains in question.

**Objective:**

The purpose of this study is to compare the practice and outcomes of CAS and CEA in a real-world setting within public university hospitals in Brazil.

**Methods:**

This study will be a prospective 5-year analysis of treatment for atherosclerotic carotid stenosis with CEA and CAS performed at 5 centers affiliated with the Vascular Study Group at public university hospitals in Brazil. The indications for the procedures will be determined by each surgeon’s individual discretion, in accordance with preoperative risk evaluation. The primary outcome measures will be (1) any in-hospital stroke or death, and (2) any per-procedural stroke, death, or myocardial infarction (MI). Patients undergoing CEA in conjunction with cardiac surgery will be excluded from the study. Multivariate logistic regression will be performed to identify predictors of stroke or death in patients undergoing CEA and CAS. All tests of significance will be performed at the .05 level. This study was approved by the Committee of Ethics in Research at the University Hospital of Ribeirao Preto Medical School, and in all other participating institutions linked to National Research System and National Board of Health in Brazil (Process 15695/2011).

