**Conclusions:**

The analyses of the primary endpoints (and all others variables of the study) are expected to be published in 2019 in a peer reviewed journal, and results will be presented at scientific meetings, with summary results published online. This study will obtain new data related to the quality of treatment for carotid disease in Brazil at the primary training centers of future vascular surgeons, but the initial data that will be obtained and published (with the outcomes and complications) are restricted to the first 30 days postprocedure. This time restriction limits the comparison of the results that relate to the main goal of treatment, which is to decrease the risk of stroke over 5 years. The purpose of the study group is to continue the monitoring of patient records, and evaluate the follow-up data in the 5 years following the initial evaluation. This study protocol will contribute very significantly to improving the care of patients with carotid disease, in addition to qualifying the level of assistance provided in public university hospitals in the state of São Paulo, Brazil.

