### Data Source and Measurement

Outcomes will be stratified by symptomatic and asymptomatic status. Symptomatic patients will be defined as having a neurological event, including any hemispheric or ocular transient ischemic attack, or major or minor stroke, that precedes the intervention ipsilateral to the treated lesion. Our definition of a symptomatic patient is the occurrence of symptoms for up to 180 days. This definition is similar to that of the Carotid Revascularization Stent Trial (CREST), although ICSS trial lesions were considered symptomatic for up to one year [1,11,12].

Technical success pertains to per-procedural events from the initiation of the procedure through the first 24-hour post operative period. Primary technical success will require the successful excision of the carotid plaque by surgical or interventional means. Technical success will be assessed by the outcomes and complications related to preoperative carotid angiograms, whenever these imaging studies are obtained prior to the carotid intervention. For CEA, primary technical success implies the successful removal of the carotid plaque and closure of the artery, with or without a patch, with less than 30% residual stenosis in the absence of stroke, MI, and death. For CAS, the introduction and deployment of the EPD and carotid stent in the absence of stroke, MI, death, surgical conversion, and vascular obstruction constitute primary technical success [13]. Secondary endpoints of interest include procedure time, blood loss, blood transfusion, clamping and shunting time, fluoroscopy time, contrast load, recovery time, range and average number of days in an intensive care unit, and length of hospital stay.

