All complications will be categorized as local vascular, local nonvascular, or systemic. Complications after carotid interventions will be reported in a systematic and standardized manner with a description of the degrees of severity. Although assigning a degree of severity to all complications arising from different treatment methods may be difficult, severity scales should be provided whenever possible to allow for the assessment and comparison of adverse events. The following severity scale has been modified from the reporting standards for lower extremity ischemia established by Rutherford et al [14]: *Mild* (level 1) refers to a complication that resolves spontaneously or with minimal intervention, does not increase the length of hospital stay, and does not cause permanent disability. *Moderate* (level 2) refers to the need for significant intervention, an extension of hospitalization beyond 24 hours, and, at most, minor permanent disability that does not interfere with normal daily activity. A *severe* complication (level 3) requires major surgical, endovascular, or medical intervention, may be associated with prolonged convalescence, is usually accompanied by prolonged or permanent disability, and may result in death. Prehospital discharge data related to stroke/death will be recorded, as applicable.

When obtaining patient consent, the patient will first be approached by a doctor who is a member of the treatment team at the same hospital in which the patient will be receiving treatment. Upon obtaining patient consent, we will record the patient name, patient signature, date of signature, and the name of the doctor who introduced the study to the patient, as well as his/her professional number and signature.

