## Results

The study is in the recruitment phase, and we are enrolling patients at 5 centers in Brazil. It is anticipated that 800 patients will be recruited to the study by the end of 2018. Analyses will focus on primary end points for patients that are allocated to each treatment group. During the per-procedural period, the occurrence of the primary end point components (stroke, MI, or death) for CAS and CEA will be analyzed for symptomatic or asymptomatic subjects. The median time from randomization to the procedure will be compared for CAS and CEA. Stenting with embolic protection of patients will be assigned to the CAS group. General or local anesthesia of patients will be assigned to the CEA group. The median duration of follow-up will be determined. During that time, the level or prevalence of selected risk factors will be analyzed to determine if they remained similar between the two treatment groups.

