One meta-analysis pooled data from 13 prospective, randomized, or controlled clinical trials that compared CEA with CAS [18]. With combined data from all trials, over 7000 patients were included, the majority of whom (79%) were symptomatic. The post operative risk of stroke and death over the subsequent 30 days was higher in the CAS group compared with the CEA group (odds ratio [OR] 1.57, *P*=.01) and was highest in symptomatic patients (OR 1.89, *P*=.01). EPDs used with CAS did not significantly reduce the 30-day per-procedural risk of stroke/death related to CEA, but they did decrease the 30-day risk of stroke/death compared to that associated with CAS without an EPD (2.7% vs 7.5%, OR 0.34, *P*<.01). In contrast, CAS was associated with a lower risk of cranial neuropathy (OR 0.06, *P*<.01) and a lower risk of post operative MI (OR 0.43, *P*<.01). Based on these findings, the authors advocated reserving CAS for revascularization in patients with anatomical conditions that make CEA difficult or place patients at higher risk for cranial nerve injury (such as restenosis after prior CEA), or in patients with concomitant significant carotid artery disease. The limitation of CAS to specific patient groups is outlined in both the Society of Vascular Surgery and European Society of Vascular Surgery guidelines, particularly for those at high risk for CEA and in, “high-volume centers with documented low per-procedural stroke and death rates or inside a randomized clinical trial” [19,20].

Some other important studies are underway. In response to the growing uncertainty regarding clinical management of asymptomatic patients with carotid artery disease, the National Institutes of Health is financing the CREST-2 trial. This multicenter, randomized study has two arms related to intervention: CEA versus best medical therapy (BMT) and CAS versus BMT. Patients can opt to enroll in either the CEA or CAS arm. Randomization, therefore, determines whether a patient undergoes an intervention or BMT, rather than the type of intervention (CEA or CAS). Patients allocated to CEA or CAS treatments will also receive the same BMT as those randomized to medical treatments. The study is expected to take approximately 10 years to complete randomization, and produce results for at least 4 years of follow-up [21].

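### Primary outcome (1) stops at discharge and the per-procedural window of outcome (2) is never fixed; both should run from procedure start to day 30

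*Protocol article*

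**What the plan says.** The Abstract (Methods) sets two primary outcomes: "The primary outcome measures will be (1) any in-hospital stroke or death, and (2) any per-procedural stroke, death, or myocardial infarction (MI)". The setting of the first is the hospital stay. The second carries no time limit there.

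Four other places bear on the windows:

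- *Data Source and Measurement*, on technical success: "Technical success pertains to per-procedural events from the initiation of the procedure through the first 24-hour post operative period".
- *Discussion*, reporting a published meta-analysis: "EPDs used with CAS did not significantly reduce the 30-day per-procedural risk of stroke/death related to CEA".
- *Abstract, Conclusions*, on the initial outcome and complication data of this study: they "are restricted to the first 30 days postprocedure".
- *Data Source and Measurement*, on recording: "Prehospital discharge data related to stroke/death will be recorded, as applicable".

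The *Results* section makes the per-procedural period the basis of the main comparison without giving its length: "During the per-procedural period, the occurrence of the primary end point components (stroke, MI, or death) for CAS and CEA will be analyzed". Time in hospital is itself a secondary endpoint: "range and average number of days in an intensive care unit, and length of hospital stay".

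**The concern.** An outcome that ends at discharge gives each patient a different time at risk. The procedure here is chosen at the surgeon's discretion with regard to preoperative risk (Abstract, Methods), and comparing the two procedures is the stated objective. If one group tends to go home sooner, fewer of its events can be counted at the same true risk, and it looks safer than it is. Adjusting for baseline covariates does not restore events that the outcome definition excludes.

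The second outcome has a different weakness. The article attaches two spans to one word and does not say which applies to the outcome. Two analysts could therefore count different events for the same primary outcome.

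The article's own benchmarks are 30-day figures: 7.4% for CAS against 4.0% for CEA for stroke, death or myocardial infarction (Introduction), and an odds ratio of 1.57 for stroke or death (Discussion). A discharge-limited outcome is not on the same footing, and whether outcome (2) is depends on a definition that the article does not give.

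**Working it through.** **Windows side by side**

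| Item | Window in the article | Applies to |
|---|---|---|
| Primary outcome (1) | Until discharge | Stroke or death |
| Primary outcome (2) | *Per-procedural*, no length given | Stroke, death or MI |
| Technical success | Procedure start to 24 hours | A separate endpoint |
| Cited meta-analysis | 30 days, called per-procedural | Other studies |
| Initial data of this study | 30 days | Outcomes and complications |

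**What each reading counts**

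| Event | Outcome (1) | Outcome (2) if 24 hours | Outcome (2) if 30 days |
|---|---|---|---|
| Stroke on day 2, still in hospital | Yes | No | Yes |
| Stroke on day 10, after discharge | No | No | Yes |

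Outcome (1) excludes the day-10 event on any reading. For outcome (2), the reading decides both rows.

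**How far a discharge cut-off could move the comparison.** The article states no figure to reproduce: it gives no stay by procedure and no event timing. Everything in this step is assumed.

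Let the true 30-day risk be equal in both groups. Let a share s of the 30-day events fall on day 0 and the remainder decay exponentially with mean m days, truncated at day 30. The share counted when discharge is on day d is

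f(d) = s + (1 − s) × (1 − exp(−d/m)) / (1 − exp(−30/m)).

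With s = 0.6 and m = 5:

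- f(1) = 0.673, f(3) = 0.781, f(5) = 0.853.
- Day 1 against day 3: 0.673 / 0.781 = 0.86.
- Day 1 against day 5: 0.673 / 0.853 = 0.79.
- Same discharge day in both groups: 1.00.

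Varying s over 0.5, 0.6 and 0.7 and m over 3, 5 and 10 days, the spurious risk ratio runs from 0.79 to 0.93 (day 1 against day 3) and from 0.71 to 0.89 (day 1 against day 5). Milder assumptions shrink it: day 1 against day 2 in the base case gives 0.92, and s = 0.8 with m = 5 gives 0.94 for day 1 against day 3.

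**The same effect on a true difference.** Take the 30-day rates cited in the Introduction, 7.4% and 4.0%, purely as an illustration (they include MI, which outcome (1) does not). The true risk ratio is 7.4 / 4.0 = 1.85. The counted ratio is (7.4 × c₁) / (4.0 × c₂), where c₁ and c₂ are the assumed shares of CAS and CEA events that occur before discharge.

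| c₁ (CAS) / c₂ (CEA) | Counted rates | Risk ratio |
|---|---|---|
| 80% / 80% | 5.92% v 3.20% | 1.85 |
| 70% / 80% | 5.18% v 3.20% | 1.62 |
| 60% / 80% | 4.44% v 3.20% | 1.39 |

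Equal capture loses events but leaves the ratio alone. Unequal capture moves it.

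**The case against.** The strongest defence is that the article can be read coherently. The 24-hour span is the window of technical success, and nothing applies it to primary outcome (2). The 30-day statement in the Conclusions comes just after a mention of the primary endpoints, and the Discussion pairs the word with 30 days. If *per-procedural* means 30 days, outcome (2) contains outcome (1), counts strokes at home, and has the same window as the cited 30-day rates. Two primary outcomes may also have different windows by design, and in-hospital stroke or death is a recognisable registry endpoint. A condensed article may leave the length of a named period to the full protocol.

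Much of this stands, and it rules out several stronger conclusions that a reader might infer:

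- *That outcome (2) stops at 24 hours, so both primary outcomes miss post-discharge events.* This borrows the window of another endpoint. The text leaves the span open; it does not set it at 24 hours.
- *That the windows contradict one another.* Differing windows for different outcomes are not a contradiction.
- *That stay is expected to differ by procedure.* Length of stay is only listed as a secondary endpoint. The Introduction calls CAS less invasive but says nothing about stay.
- *That only pre-discharge events will be recorded.* The recording sentence does not say so and does not exclude the 30-day data.

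Two things survive. Outcome (1) ends at discharge on every reading. And the article does more than stay silent on outcome (2): it uses the word with two different spans, so a reader cannot tell which one governs.

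**Conclusion.** The point holds in a limited form. Outcome (1) has an observation time that can vary by procedure in a non-randomised comparison, and it leaves out events after discharge that fall inside the 30 days of data the article says it will have. Outcome (2) needs a stated window.

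Whether outcome (1) is biased, in which direction and by how much cannot be determined from the article. If stay differs, the group discharged earlier is favoured. The illustrative risk ratios of 0.71 to 0.93 rest on assumed event timing and on assumed gaps of 2 to 4 days in stay; with equal stay the figure is 1.00. They show that the effect could matter and are not an estimate of it.

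This is an inexpensive improvement to the primary outcome definitions. It does not show that the planned comparison is invalid.

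**What to change.** 1. Count both primary outcomes (stroke or death; stroke, death or MI) from procedure start to day 30 in both groups, whether or not the patient has been discharged.
2. Define *per-procedural* once, as that period, for these outcomes. Keep the 24-hour window for technical success only, and say so.
3. Report in-hospital events as a descriptive split of the 30-day outcomes.
4. State that stroke, death and MI status is ascertained to day 30, so that the sentence on recording before discharge is not taken as the limit.

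The cost is mainly wording, because the Abstract's Conclusions already commit to 30-day data. The downside is that some patients may lack day-30 status. Their number should be reported by procedure, and the rule for handling them set before the data are analysed.

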**Results:**

This study is currently in the recruitment phase, and the final patient is expected to be enrolled by the end of 2018. We hope to recruit approximately 800 patients to the study. Analyses will focus on primary end points for patients that are allocated to each treatment group. During the per-procedural period, the occurrence of the primary end point components (stroke, MI, or death) for CAS and CEA will be analyzed for symptomatic or asymptomatic subjects.

**Conclusions:**

The analyses of the primary endpoints (and all others variables of the study) are expected to be published in 2019 in a peer reviewed journal, and results will be presented at scientific meetings, with summary results published online. This study will obtain new data related to the quality of treatment for carotid disease in Brazil at the primary training centers of future vascular surgeons, but the initial data that will be obtained and published (with the outcomes and complications) are restricted to the first 30 days postprocedure. This time restriction limits the comparison of the results that relate to the main goal of treatment, which is to decrease the risk of stroke over 5 years. The purpose of the study group is to continue the monitoring of patient records, and evaluate the follow-up data in the 5 years following the initial evaluation. This study protocol will contribute very significantly to improving the care of patients with carotid disease, in addition to qualifying the level of assistance provided in public university hospitals in the state of São Paulo, Brazil.

**Trial Registration:**

Clinicaltrials.gov NCT02538276; https://www.clinicaltrials.gov/ct2/show/NCT02538276 (Archived by WebCite at http://www.webcitation.org/6m7APnFLD)

## Introduction

Cerebrovascular disease is a leading cause of serious long-term disability and death [1,2]. A significant proportion of ischemic strokes originate from the atherosclerosis of extracranial arteries. In most cases, carotid endarterectomy (CEA) or stent angioplasty of the carotid bifurcation is considered when color duplex ultrasound detects clinically significant extracranial internal carotid artery stenosis. However, several clinical situations exist in which other imaging techniques are needed to provide greater anatomical detail and resolution.

Revascularization of severely atherosclerotic carotid arteries has been shown to be safe and effective in the prevention of stroke [2-5]. Carotid artery stenting (CAS) and CEA are two alternative methods of revascularization, and these techniques have been compared in small randomized clinical trials [6-10]. In the 2010 International Carotid Stenting Study (ICSS), 1713 symptomatic patients from 50 centers in Europe, Australia, New Zealand, and Canada were prospectively randomized to a CAS or CEA condition. The 30-day results showed a combined stroke, death, and myocardial infarction (MI) rate of 7.4% for CAS and 4.0% for CEA (*P*<.006). This effect was primarily driven by an increased stroke rate of 7.0% for CAS versus 3.3% for CEA [1].

Although randomized trials provide the most scientifically valid comparisons between treatments, they do not reflect the diversity of patients or technical proficiency present in broad contemporary clinical practice. CEA has been considered the first-line treatment for carotid stenosis worldwide, and the safety and efficacy of CAS compared to CEA remains in question. CAS is officially approved for use in multiple countries, and the number of patients undergoing CAS has been increasing due to its less-invasive nature. The present study aims to demonstrate the real-world status of the treatment of carotid artery disease with CAS and CEA using the prospective registry of vascular diseases of university hospitals in the state of Sao Paulo, Brazil, called the RHEUNI (Registry Project of Vascular Disease in the Public University Hospitals of São Paulo). It is well known that no prospective studies with a significant number of cases concerning the treatment of carotid disease exist in Brazil; all available data were derived from studies conducted in other countries. Thus, the main objective of this study is to evaluate the quality of treatment for carotid disease in Brazil by analyzing the two main techniques currently available. The data will be derived from the vascular surgery centers that bear primary responsibility for the training of future vascular surgeons.

## Methods

### Patient Population and Setting

The CEA and CAS registry in Brazil (part of RHEUNI) is being used as a prospective observational study in Brazil, and has been conducted since July 2013. Final data analyses are expected in July 2018 from the 5 public university hospitals of the São Paulo state that provide vascular therapy. Several consecutive procedures will be registered as CEA or CAS by certified vascular surgeons from 5 centers (University Hospital of Ribeirão Preto Medical School of University of São Paulo, University Hospital of School of Medical Sciences of University of Campinas, University Hospital of Marilia Medical School, University Hospital of Botucatu Medical School, and University Hospital of São Jose do Rio Preto Medical School). All participating vascular surgical centers have extensive experience in the treatment of carotid disease, and they are all training centers of reference in Brazil. The ethical committee of each hospital has approved this project.

Inclusion criteria are as follows: patients with carotid atherosclerotic stenosis >70% who underwent CEA or CAS for the treatment of carotid stenosis at any of the 5 hospitals involved in the study, male or female, and >18 years of age. Carotid stenosis is defined as (1) stenosis >70% by catheter angiography (North American Symptomatic Carotid Endarterectomy Trial criteria) or (2) by Doppler ultrasound with >70% stenosis defined by a peak systolic velocity of at least 230 cm/second, plus at least one of the following: an end diastolic velocity >100 cm/second, or internal carotid/common carotid artery peak systolic velocity ratio >4.0, or computer tomography with >70% stenosis, or magnetic resonance with >70% stenosis. Exclusion criteria include cases of concomitant cardiac surgery, carotid dissection, fibromuscular dysplasia, or trauma.

RHEUNI data have been validated for completeness by quarterly audits of discharge claims data from each participating institution. These audits ensure complete inclusion of all consecutive procedures performed at the participating hospitals.

